## **19.2 Trial committees**

### **19.2.1 Trial Coordinating Committee (TCC)**

The supervision of the trial will be a responsibility of the Trial Coordinating Committee (TCC). The members will include the 2 Principal Investigators, study directors, clinical coordinators, representative from WRAIR, laboratory coordinators, study nurse and data manager. The TCC will be meeting at least once a week during the trial period. The TCC will prepare a monthly report for presentation at the TaMoVac steering committee meeting. This committee will be responsible for decisions about grade of adverse events and relationship to study vaccine. The final decisions on grading of AE and relationship with vaccine may be ascertained by an independent End-Point Committee. Notes of meetings will be kept, and the Committee will report to the TaMoVac Steering Committee. The trial may be suspended by this Committee for any reason, including on the recommendation of the DSMB.

### **19.2.2 Trial Management Group (TMG)**

This group will oversee the day-to-day running of the trial and the members will be primarily the clinical and data management teams. The members will be among others, the site PI, clinical coordinator, laboratory coordinator, study Pharmacist, study nurse and data manager. The lab manager will join if there are relevant items on the agenda. Notes will be taken and will form the basis of the progress report to the Trial Coordinating Committee. Each site will have its own TMG.

### **19.2.3 TaMoVac Steering committee**

The TaMoVac Steering committee will review the notes from the TCC meetings regarding progress of the trial, and will be meeting/communicating once a month. The committee will have an independent chair and a secretary and advise the sponsor on the conduct of the study. The steering committee may initiate an interim analysis provided blinding is maintained..

## **19.3 Data and Safety Monitoring Board (DSMB)**

An independent Data and Safety Monitoring Board will be appointed by the sponsor of the study, MUHAS and SMI. The role of the DSMB will include:

1. To review the research design and the plans for data and safety monitoring
2. To receive and review at intervals the progress reports from the investigators
3. To monitor safety data
4. To monitor and evaluate trial progress, including
  - a. Periodic assessment of data quality and timelines
  - b. Performance of the study sites
5. To recommend to the sponsor, local IRB's and investigator concerning continuation or to stop the study.

The DSMB will meet whenever a safety report has been submitted and make a recommendation to the TCC within 7 days as to the future conduct of the trial.

They will also meet on one occasion to review the safety data, after half the volunteers have received the first immunization in order to make recommendations to the sponsors of the study.

## **19.4 Community Advisory Board (CAB)**

At each study site there will be a Community Advisory Board drawing representative members from the Police Force and general population in Dar es Salaam and representative members from the general population in Mbeya. There may also be members from the media, legal representation and study participants. In Mbeya a CAB has been established since 2005 and

regular meetings are ongoing since then concerning current and past research activities. In Dar es Salaam the CAB will meet before the onset of the study for a general study information session, discussion of recruitment strategies, outreach activities and tracing, participant identification, insurance, and compensation issues. The CAB will be informed in detail about benefits and risks concerning study participation, informed consent procedures as well as HIV risk questioners. The purpose of this meeting is also to receive comments about the comprehensibility and clarity of the proposed participant study information/briefing sessions and informed consent procedures. Regular CAB meetings will then be held at 3 monthly intervals throughout the trial. Up-dates or changes of the study status and information of general HIV Vaccine related issues (e.g. STEP trial) will be provided for the CAB members. Problems concerning individual study participants also in respect to community related topics (e.g. stigmatization) will be discussed in an anonymous fashion and additional CAB meetings might be called at any time in the case of special circumstances.

In addition, the wider Tanzanian community has since the first high profile National HIV Vaccine Strategy Plan Workshop held in Bagamoyo in 2001 been informed through the mass media on the need and on plans for HIV vaccine trials in Tanzania. The public will continue to be informed through press releases and through other channels on all the stages of the TaMoVac trial.

### **19.5 Indication for additional review**

There will be an additional meeting of the DSMB if 3 or more volunteers experience an unexplained, unexpected grade 3 or 4 clinical or laboratory event (confirmed on attendance or repeat testing) not resolved within 72 hours and considered probably or possible and likely to be related to vaccine product.

## **20 STATISTICAL CONSIDERATIONS**

By the end of this study 120 study participants will have been exposed to DNA or placebo as well as MVA or saline placebo and described in the quantitative and qualitative immunogenicity and safety evaluation.

The sample size for this study is similar to other Phase 1 safety and immunogenicity studies of vaccines published in the literature. In the primary analysis, the results of the IFN-gamma ELISpot 2 weeks after the second MVA will be used as the primary endpoint. We expect 100% of those in group IIIA (controls) to be responders. We will need 36 in each group to be able to detect a 20% difference in either group IA or IIA, with a power of 80% and 5% significance level (one sided). In each vaccine group, 4 volunteers will be assigned to receive placebo. Statistical significance may not be attained with such low power but would provide justification of the need for a study with greater power. The sample size will allow preliminary evaluation of between-group variability.

### **20.1 Analysis**

All safety end-points will be graded by the Clinical Investigator and reviewed by the Trial Management Group. Any queries about grade and relationship to study product that cannot be resolved will be referred to the Trial Coordinating Committee for a final decision.

The primary safety end-points are: The safety of immunization with the seven DNA plasmids carrying HIV-1 genes as assessed by clinical signs, and standard clinical chemistry/hematological laboratory tests where any worsening of the severity grade will be considered for causality by the vaccine.

The alternative immunization applications (2x i.d. versus 5x i.d. with the Biojector device) will be evaluated for adverse events by assessing local (pain, cutaneous including indurations),

general (fever, chills, headache, nausea, arthralgia, malaise, myalgia) and other unsolicited adverse events within 7 days.

#### *Immunogenicity endpoints*

The primary immunogenicity endpoint is the frequency, magnitude and quality of HIV-specific cellular immune responses determined by the IFN- $\gamma$  ELISPOT assay.

The secondary immunogenicity endpoints include cellular immune responses determined by ICS and T cell proliferative responses and antibody responses determined by binding and neutralizing antibody assays.

### **20.2 Statistical analysis**

The final analysis will be conducted once all study participants have received all their immunizations and completed the 84 weeks follow-up period, or have permanently withdrawn from the study. Safety analyses will further be updated in the event that there is 108 weeks follow up. Analyses will be based on the principle of intention-to-treat. Interim analysis of safety and immunogenicity may be performed if measures are taken to maintain blinding.

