
### **8.3 Enrolment and Vaccination I (1st DNA/Placebo) (Study Visit 3, week 0)**

The study volunteer again meets both study nurse(s) and study doctor(s) (**CRF 2-II**). Confirmation has to be made and recorded that the volunteer fulfils all inclusion/exclusion criteria including laboratory results (**CRF 5-II**) and eligibility criteria (**CRF 5-III**). If a volunteer is not found to be eligible a Screening Outcome Form (**CRF 5-IV**) will be filled indicating reasons for ineligibility. Enough time has to be planned for the visit so that all questions from the volunteer about the study can be answered or reflected upon. A senior Physician will confirm if the volunteer understands the concepts of the study and will also assess the willingness and voluntariness the study volunteer. As indicated during the informed consent procedure the volunteer had consented on a study photo identification card produced and provided by the site. This photo ID will be kept by the study participant and will have to be

presented at each study clinic contact for identification purposes, unless other unequivocal identification can be documented.

For enrolment the initial screening number will be used as the study number. This means that study numbers may be discontinuous. The participant will then be randomized into one of the study Groups.

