#### **8.22 In the event of study discontinuation**

Study volunteer/participants may withdraw his/her consent to participate in the study at any time without prejudice. Wherever possible, the tests and evaluations listed for the termination visit will be carried out if the volunteer/participant refuses follow-up according to the protocol visit schedule. The study monitor and Data and Safety Monitoring Board (DSMB) will be notified of all study withdrawals within 2 working days for enrolled participants.

Volunteers/participants who withdraw from the study will be replaced only as long as the study is still open for enrolment. No replacement will be allowed when the enrolment is closed. All participants who receive at least one immunization will be included in the safety analysis. If a participant does not complete the immunization schedule secondary to a serious adverse event or toxicity, he or she will continue to be followed according to the protocol visit schedule, and, at a minimum, until the adverse event/toxicity is resolved and/or the cause is identified.

A genuine effort will be made to determine the reason(s) why a volunteer fails to return for the necessary visits. This information will be recorded on the Subject Status Form (**CRF 7-I**).

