### **20.4 Safety data**

The number and percentage of subjects experiencing any adverse events (AE), grade 3 or 4 adverse events, serious adverse events (SAE), and the number of events reported, will be summarized by severity and reported relationship to study treatment for each treatment group, both for all adverse events and by type of adverse event. Calculation of incidence rates of adverse events will include each subject only once, either according to worst severity or first reported event.

Rates of the various adverse events will be compared between the study Groups using Fisher's exact test. Rates will be summarized using exact binomial confidence intervals

Safety hematological and clinical chemistry laboratory parameters will be summarized at each study visit according to study Group. Comparisons will be done using 2-sample t-tests or non-parametric equivalents as appropriate to the data

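### The intention-to-treat rule in Protocol section 20.2 also covers safety, so reactions after a misadministration would be counted under a product not received; it should be reconciled with section 8.22

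*Protocol*

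**What the plan says.** Section 20.2 gives one analysis principle: "Analyses will be based on the principle of intention-to-treat". The sentence before it concerns safety: "Safety analyses will further be updated in the event that there is 108 weeks follow up". The sentence after it concerns both kinds of data: "Interim analysis of safety and immunogenicity may be performed if measures are taken to maintain blinding". Nothing in the section limits the principle to immunogenicity.

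Section 20.4 tabulates adverse events by severity and "reported relationship to study treatment for each treatment group, both for all adverse events and by type of adverse event". It adds that "Rates of the various adverse events will be compared between the study Groups using Fisher's exact test" and that "Rates will be summarized using exact binomial confidence intervals". It does not define group as assigned or as received.

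Section 8.22 sets an inclusion rule based on exposure: "All participants who receive at least one immunization will be included in the safety analysis".

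Section 8.3, describing visit 3, says "The participant will then be randomized into one of the study Groups". The medical check and pregnancy test that must precede the first injection are described afterwards, in section 8.3.3.

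**The concern.** Safety of the DNA/MVA regimen at two DNA doses is the first primary objective (sections 2.1 and 5.1). That is a question about exposure: what happens to people who receive a given product and dose. Grouping by assignment suits a comparison of randomised groups. For safety, it credits or charges a product with events in people who did not receive it.

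The placebo groups are very small, so one misclassified volunteer can change or even reverse the apparent comparison. A swap between vaccine groups would blur the contrast between the 600 µg and 1000 µg regimens, or between combined and separate pools. A swap would also be hard to see in the clinic. The pharmacist draws up the syringes (section 8.3.2), and clinic staff are told only whether a volunteer has two or five DNA injections (section 8.3.1). Groups I and II have the same number and volume of injections.

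The population is a second, smaller matter. A volunteer who is randomised and then fails a pre-injection check belongs to an intention-to-treat set but is not among those section 8.22 describes.

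**Working it through.** **Group sizes.** Section 8.3.1 gives each of two sites 6 sets of 10 envelopes. Each set holds 3 assignments to each vaccine group and 1 placebo.
- Per vaccine group: 6 × 3 × 2 = 36, or 108 over three groups.
- Placebo: 6 × 1 × 2 = 12, or 4 per group.

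These agree with the table in section 6.5. The point disputes no figure in the plan and leaves the sample size of 36 per group unchanged.

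**One placebo-assigned volunteer given vaccine throughout.** Assume this volunteer has one grade 3 reaction and nobody else has an event. Intervals are 95% exact binomial, as section 20.4 specifies.

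| Grouping | Placebo | Vaccine |
|---|---|---|
| As assigned | 1/12 = 8.3% (0.2 to 38.5) | 0/108 = 0% (0 to 3.4) |
| As received | 0/11 = 0% (0 to 28.5) | 1/109 = 0.9% (0.02 to 5.0) |

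Within a single placebo group the figures are 1/4 = 25% (0.6 to 80.6) as assigned and 0/3 = 0% (0 to 70.8) as received.

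**One wrong session out of five.** This is a mixed exposure. As assigned, the table still reads 1/12 and 0/108. Under the fix below the volunteer is listed separately, leaving 0/11 and 0/108 plus one listed case.

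**One swap between vaccine groups, given throughout, with one reaction.** As assigned, the volunteer's own group shows 1/36 = 2.8% and the other 0/36. As received, they show 0/35 and 1/37 = 2.7%.

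**How often this could arise.** Planned sessions: 120 volunteers × 5 = 600. Placebo sessions: 12 × 5 = 60. Vaccine sessions: 108 × 5 = 540. The protocol gives no error rate. Assuming 0.2% to 1% per session:
- Placebo: 60 × 0.002 = 0.12 to 60 × 0.01 = 0.6 expected errors in the whole trial.
- Vaccine: 540 × 0.002 = 1.1 to 540 × 0.01 = 5.4, in groups where one volunteer is 1/36 = 2.8 points.

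**Population.** If one volunteer in a vaccine group is randomised but never injected, the denominator is 36 under intention-to-treat and 35 under section 8.22. One event then gives 1/36 = 2.8% or 1/35 = 2.9%.

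**The case against.** The strongest reply is that section 8.22 is the specific rule for safety and section 20.2 only a general principle, so the specific rule governs. A reader might infer that the two sections contradict each other outright. The text does not support that. Section 8.22 says who is included and does not say that uninjected volunteers are excluded. The difference would also be small: eligibility is confirmed before randomisation (section 8.3), and adverse events are counted only after vaccination (section 14.1), so an uninjected volunteer affects only the denominator. This reply settles the population at most. Section 8.22 does not say how injected volunteers are grouped.

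A second reply is that the handling of a misdosed volunteer belongs in the statistical analysis plan. That would hold had the protocol been silent. It states a principle for all analyses, and a plan that grouped safety by product received would depart from it.

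A third reply is that the protocol guards against error. Section 10.3 requires a two-person check of the vial label before administration, and section 15 requires deviations to be recorded and reported within 2 working days. This stands, and it makes errors unlikely. A reader might set the 25-point shift in a placebo group beside an error count over all 600 sessions (1.2 to 6 at the assumed rates) and conclude that large distortions are likely. That pairing is wrong: the large shift applies only to the 60 placebo sessions, and the volunteer must also have a reaction. The safeguards do not say how an error that does occur is to be analysed.

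**Conclusion.** The point holds as a conditional defect in a stated rule. Section 20.2 makes assignment the basis of the safety analysis, and nothing elsewhere replaces it with product received. If one placebo-assigned volunteer receives vaccine throughout and reacts, the comparison reads 8.3% against 0% as assigned and 0% against 0.9% as received. An error between vaccine groups moves about 2.8 points from one group to another.

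These sizes rest on one hypothetical misadministration with no other events. The documents predict no such error, and the per-session rates used above are assumptions. Sections 20.2 and 8.22 are mismatched and need reconciling, but they are not in strict contradiction. The change is worth making because it protects a primary objective at almost no cost.

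**What to change.** In section 20.2, limit the intention-to-treat sentence to the immunogenicity comparisons. Then state that safety is analysed in all volunteers with at least one immunization, as in section 8.22, grouped by product and dose actually received, with anyone exposed to more than one regimen listed separately. Cross-refer to this from section 20.4.

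Product received should be taken from pharmacy records (CRF 8-I, the dispensing log and the returned vials) and from the deviation form CRF 7-II. CRF 10-I is not enough, because it is completed by clinic staff who are blinded to vaccine versus placebo and could not reveal a saline/vaccine swap.

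The cost is one or two sentences and a minor derivation step at analysis. No new data are needed, and the sample size and planned tests do not change.

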### **20.3 Volunteer characteristics**

Baseline characteristics will be summarized by study Groups, using appropriate summary statistics. Study participant characteristics to be summarized will include demographic variables and baseline values relevant to safety and immunogenicity.

### **20.4 Safety data**

The number and percentage of subjects experiencing any adverse events (AE), grade 3 or 4 adverse events, serious adverse events (SAE), and the number of events reported, will be summarized by severity and reported relationship to study treatment for each treatment group, both for all adverse events and by type of adverse event. Calculation of incidence rates of adverse events will include each subject only once, either according to worst severity or first reported event.

Rates of the various adverse events will be compared between the study Groups using Fisher's exact test. Rates will be summarized using exact binomial confidence intervals

Safety hematological and clinical chemistry laboratory parameters will be summarized at each study visit according to study Group. Comparisons will be done using 2-sample t-tests or non-parametric equivalents as appropriate to the data

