### **5.1 Primary objectives**

1. Determine safety of the DNA vaccine developed at Karolinska Institutet/SMI (HIVIS-DNA) at a dose of 600 µg or 1000 µg delivered i.d in combination with MVA-CMDR boost i.m
2. Determine immunogenicity of HIVIS-DNA at a dose of 600 µg or 1000 µg delivered i.d in combination with MVA-CMDR boost i.m.

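### Section 20.4 compares safety by study group (36 vs 36) where Section 20.1 frames it as 2x vs 5x injections (72 vs 36), names no interval for the difference, and names no use of baseline laboratory values

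*Protocol*

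**What the plan says.** Protocol Section 5.1 makes safety the first primary objective, "at a dose of 600 µg or 1000 µg delivered i.d in combination with MVA-CMDR boost i.m". Section 11.1 sets Grade 3 or above as the threshold for the primary safety parameters.

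Section 20.4 names three tools:

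- Event rates: "Rates of the various adverse events will be compared between the study Groups using Fisher's exact test".
- Precision: "Rates will be summarized using exact binomial confidence intervals". These are intervals for rates; an interval for a between-group difference is not named.
- Laboratory values, summarised at each visit by study group: "Comparisons will be done using 2-sample t-tests or non-parametric equivalents as appropriate to the data". No interval and no baseline value are mentioned.

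Section 20.1 describes the contrast differently: "The alternative immunization applications (2x i.d. versus 5x i.d. with the Biojector device) will be evaluated for adverse events", covering local, general and unsolicited events within 7 days.

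Section 6.5, headed as the definition of study groups, lists six (IA to IIIB), with 36 vaccinees in each of IA, IIA and IIIA. IA and IIA each receive two injections totalling 600 µg per priming visit; IIIA receives five totalling 1000 µg.

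**The concern.** Sections 20.1 and 20.4 point to different comparisons for the same primary objective, and nothing says which governs. Read through the definition in Section 6.5, the Fisher test sets IIIA against one two-injection group at a time and leaves half of the two-injection vaccinees out of each comparison. Read through Section 20.1, it uses all of them.

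For uncommon events this can change the answer. A p-value without an interval for the difference also does not show how large an excess remains compatible with the data.

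For laboratory values, haematology and chemistry are scheduled for everyone at Visit 3 (Appendices 2 and 3), and Section 8.3.3 places that draw before the first injection. A two-sample comparison of post-vaccination values that leaves this measurement out gives up precision already paid for.

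**Working it through.** **Inputs from the protocol.** 36 vaccinees per active group (Section 6.5). Everyone with at least one immunization is in the safety analysis (Section 8.22), so dropout does not shrink the event denominators.

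**Assumptions.** The protocol gives no planning rate for Grade 3+ events, no relevant laboratory shift, no baseline correlation, and no significance level for safety. I use two-sided 5% and show ranges. A low background rate is reasonable: Section 4.5 reports no related Grade 3 or 4 events in the Swedish trial.

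**The plan's own figure.** Section 20 says "We will need 36 in each group to be able to detect a 20% difference in either group IA or IIA", at 80% power and one-sided 5%, with 100% responders expected in IIIA. This concerns ELISPOT response; no size is given for safety. For 100% vs 80%:

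- Uncorrected n = [1.645·√(2·0.9·0.1) + 0.842·√(0.8·0.2)]² / 0.2² = 26.8.
- With continuity correction, (26.8/4)·[1 + √(1 + 4/(26.8·0.2))]² = 36.1.

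The stated 36 is therefore reproduced (37 if rounded up).

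**Event rates.** Power = Σ Bin(x; n₁, p₁)·Bin(y; n₂, p₂) over all tables with Fisher p < 0.05.

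| Assumed Grade 3+ rate, 2x vs 5x | 36 vs 36 | 72 vs 36 |
|---|---|---|
| 0% vs 10% | 15% | 71% |
| 0% vs 15% | 46% | 92% |
| 0% vs 20% | 75% | 98% |
| 2% vs 15% | 29% | 70% |
| 5% vs 15% | 15% | 37% |
| 5% vs 20% | 35% | 61% |

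The reason is visible in the critical values. Against 0/36, 5/36 gives p = 0.054 and 6/36 gives p = 0.025, so six events are needed. Against 0/72, 3/36 gives C(36,3)/C(108,3) = 7140/204156 = 0.035. Three events in IIIA and none in IA or IIA would thus give p = 0.24 against either two-injection group alone and p = 0.035 against both together.

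**What an interval adds** (Newcombe 95%). With 5/36 vs 2/36, Fisher gives p = 0.43. The difference is +8.3 points (−6.5 to +23.6), so an excess above 20 points is not excluded. With 3/36 vs 0/72, the difference is +8.3 points (+0.9 to +21.8).

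**Laboratory values.** The t-test noncentrality is d·√(n₁n₂/(n₁+n₂)). For d = 0.5 this is 0.5·√18 = 2.12 at 36 vs 36 and 0.5·√24 = 2.45 at 72 vs 36. Adjusting for a baseline with correlation r multiplies the residual SD by √(1−r²), so d becomes 0.5/√(1−r²); the one degree of freedom lost is ignored.

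| Analysis | 36 vs 36 | 72 vs 36 |
|---|---|---|
| Unadjusted | 55% | 68% |
| ANCOVA, r = 0.3 | 59% | 72% |
| ANCOVA, r = 0.5 | 68% | 80% |
| ANCOVA, r = 0.7 | 83% | 92% |
| ANCOVA, r = 0.8 | 94% | 98% |

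**The case against.** The case on the other side is substantial.

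- **The methods are valid.** Fisher's test and exact intervals suit sparse events, and a two-sample test is sound under randomisation. This stands: the point concerns efficiency and alignment, not an invalid analysis.
- **36 vs 36 is one reading.** Section 20.4 does not fix pairwise tests, and Section 8.3.1 uses the word group for the 2x/5x split. This is fair, but Section 6.5 defines study groups as IA to IIIB and Section 20.4 does not resolve the choice.
- **Pooling has an assumption.** The gain at 72 vs 36 requires IA and IIA to have similar event rates. This stands.
- **The laboratory point rests partly on silence.** Section 20.4 does not say raw values rather than changes are tested, and the primary laboratory parameter is a confirmed Grade 3+ abnormality, not a mean shift. This makes the laboratory part an improvement rather than a correction. Change scores would not remove it: their variance factor is 2(1−r) against 1−r² for ANCOVA, for example 1.00 vs 0.75 at r = 0.5 and 0.60 vs 0.51 at r = 0.7.
- **A SAP could settle all of this.** Possibly, but Sections 20.1 and 20.4 already state a contrast and named methods, and these do not line up.

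A reader might also infer that the protocol will treat a non-significant safety test as proof of equal safety. It says nothing of the kind: the objective is to determine safety, Section 20 concedes low power in general terms, and pausing and review (Sections 16.2 and 19.5) turn on graded events rather than p-values.

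**Conclusion.** The point holds as a moderate, low-cost improvement to stated methods. Moving from 36 vs 36 to 72 vs 36 raises Fisher power by 56, 46 and 26 points for 0% vs 10%, 0% vs 15% and 5% vs 20%. Baseline adjustment at r = 0.5–0.7 adds about 12 to 28 points for a 0.5-SD shift. These gains rest on assumed rates, shift and correlations, a two-sided 5% level, and similar reactogenicity in IA and IIA. If the Fisher test were one-sided, power at 36 vs 36 for the same three pairs would be 29%, 64.5% and 47%.

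Three stronger conclusions might be drawn and should not be:

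- That finding no difference is the likely result for a 0.5-SD laboratory shift. The unadjusted test misses it 45% of the time at 36 vs 36 and 32% at 72 vs 36, so detection is the likelier outcome.
- That non-significance is nearly certain for any plausible harm. At 0% vs 20%, even 36 vs 36 has 75% power.
- That the tests are the only comparative safety output. Section 20.4 also tabulates events by treatment group, severity and relationship, with exact intervals for rates; for 0/36 the upper limit is 1 − 0.025^(1/36) = 9.7%.

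**What to change.** In Section 20.4:

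1. Name two injections (IA and IIA together, n = 72) versus five (IIIA, n = 36) as the main comparative safety contrast, in line with Section 20.1. Report the Grade 3+ risk difference, 5x minus 2x, with a 95% confidence interval beside the Fisher p-value. Keep the three-group table with its exact intervals.
2. Compare laboratory values by ANCOVA adjusted for the Visit 3 value, giving the adjusted difference with a 95% interval. Transform, or use a rank-based version, where the distribution is skewed.

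The cost is analysis wording; no visit, sample or participant is added. The one real downside is that pooling assumes combined and separate plasmid pools have similar reactogenicity, which the retained three-group table lets readers check.
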